
#### Primary outcome measure

The primary outcome measure is change between baseline and 6‐month follow‐up in self‐reported weekly alcohol consumption estimated over the last month, in UK standard units. Change in weekly alcohol consumption will be derived from the extended quantity‐frequency questions of the AUDIT [34], adjusting for heavy episodic use (question 3 of the AUDIT) and therefore allocating an individual to a category of consumption that is closest to their actual consumption. The AUDIT‐C questions exhibit similar sensitivity and specificity to the full AUDIT [35] and have demonstrated excellent reliability and responsiveness to short‐term change [36]. The extended AUDIT‐C is a variant of the AUDIT‐C, which has a greater range of response options (seven instead of five) on the quantity and frequency items, therefore improving the granularity of the information collected. This method of deriving alcohol consumption has been used in other trials [37, 38, 39, 40] and has high levels of agreement in levels of self‐reported consumption when compared with other retrospective daily diary measures [41]. This measure minimises response burden on participants because of its brevity, which is a critical issue in digital trials that have minimal contact with participants and can suffer from high levels of attrition [42].

#### Secondary outcome measures

Change between baseline and 1‐ and 3‐month follow‐ups in self‐reported weekly alcohol consumption estimated over the last 1 and 2 months, respectively;Heavy episodic alcohol use (measured using AUDIT question 3) at 6‐month follow‐upProportion of hazardous drinkers (AUDIT score ≥8);Alcohol‐related problems or consequences and alcohol‐related injury (measured using the Alcohol Short Index of Problems) [43] at 6‐month follow‐up;Use of healthcare services (measured using the Service Use Questionnaire) [44, 45] at 6‐month follow‐up;Health‐related quality of life (measured using the EQ‐5D‐5L) at 6‐month follow‐up.

The self‐report AUDIT questionnaire has 10 items that measure alcohol consumption, harms and dependence. The AUDIT is a reliable and standardised alcohol‐related outcome measure that is commonly used in alcohol trials [5, 23]. It has a high test–retest reliability when completed online [46], allows the derivation of a core outcome set for consistency across trials and minimises research waste and selective reporting [47]. The timeframe of the AUDIT will be modified to refer to the past 6 months when asked at the 6‐month follow‐up so this can be directly compared with the baseline AUDIT, which will also refer to the past 6 months. The extended AUDIT‐C when asked at the 1‐ and 3‐month follow‐up will refer to the past 1 month and 2 months, respectively, to capture participants’ alcohol consumption since the last survey.

#### Process measures

The mixed‐methods process evaluation involves assessing psychological measures, engagement and acceptability.

Psychological measures will be assessed as potential mechanisms of action at baseline and 6‐month follow‐up using four theoretical measures: urges to drink; motivation to drink less; self‐regulatory and self‐monitoring capacity (see Fig. 1 for the Logic Model). Strength of urges to drink will be measured by the question ‘How strongly have you felt the urge to drink alcohol in the past 24 hours?’ with six options from ‘Not at all’ to ‘Extremely strong’. The strength of urges to drink measure has been chosen because it can be done through a single item question and has fair long‐term test–retest reliability [48]. The motivation to drink less will be measured with the single‐item motivation to stop scale (MTSS). The MTSS and the urges to drink measure are both used in the Alcohol Toolkit Study allowing for national comparisons and have been successfully used in an observational study that estimates patterns of alcohol consumption and reduction in a sample in England [49]. Self‐regulatory capacity will be measured by ‘How difficult do you find it to control your drinking?’ using a 5‐point scale from ‘Not at all’ to ‘Extremely’. Self‐monitoring capacity will be measured by ‘How often, if at all, do you keep track of how many units of alcohol you personally drink each week?’ ranging from ‘Never’ to ‘Always’.

Engagement with Drink Less will be assessed in terms of app download, frequency, amount, duration and depth of engagement [50]—all automatically recorded within the app, among participants in the intervention group. This will provide objective data on how participants interact with the app. App download will be assessed by whether the participant downloaded and opened Drink Less (a binary yes/no measure). Frequency of engagement will be assessed by number of sessions, where a new session is defined as a new screen view after 30 minutes of inactivity [51]. Amount of engagement will be assessed by time on app in minutes. Duration of engagement will be assessed by number of days used. Depth of engagement will be assessed by the percentage of available screens viewed. Participants will also be asked about their use of the app in the semi‐structured interviews to complement and enhance the patterns identified from the objective engagement data. For example: ‘Can you tell me about your experience of using the app?’ and ‘In what situations did you use it and why?’ Adherence to either the intervention or comparator will be measured at 1‐month follow‐up with the self‐report question ‘Did you look at or use the digital tool we recommended?’ with options Yes/No. Participants are informed that their answer itself does not matter and that they are still eligible to take part, but that their answer will help the researchers to draw more accurate conclusions.

The acceptability of the intervention will be assessed in a number of short semi‐structured interviews among a sub‐sample of participants in both the intervention and comparator group after the 6‐month follow‐up. The interview will focus on perceptions of the intervention in terms of the acceptability of the app—the extent to that participants consider the app to be appropriate, based on anticipated or experienced cognitive and emotional responses to the intervention [52]. The interview topic guide will be based on the Theoretical Framework of Acceptability [52].

#### Economic measures

Unit costs for the economic evaluation will be taken from standard sources (e.g. Personal Social Services Research Unit [PSSRU] and NHS tariffs).

### Data management and monitoring

Baseline and follow‐up assessment data will be collected online in Qualtrics and then held securely in Data Safe Haven. All personal data will be pseudonymised. Engagement data will be collected automatically from the app and downloaded via python/pandas script into Data Safe Haven from a secure https protocol and ‘Nodechef’ (an online platform for hosting mobile apps). The audio recording of the semi‐structured interviews on acceptability will be pseudonymised and transferred directly from the recording device to Data Safe Haven. Any participant who opts out of the study will have their data deleted.

An independent data monitoring committee will have access to the unblinded comparative data and will monitor these data. The committee will make recommendations on whether there are any reasons to terminate the trial that the chair will report to the independent trial steering committee.

### Analysis

The data will be analysed using R Studio [53]. The data analyst will be blinded to participants' group and the analysis plan will be finalised and uploaded onto Open Science Framework before the start of data analysis when the trial will be analysed in accordance with the pre‐specified plan.

Descriptive statistics of participants' sociodemographic characteristics and AUDIT score will be reported for whom the study recruited and who then accessed the intervention. The difference between the intervention and comparator groups on baseline characteristics will be assessed using one‐way ANOVAs for continuous variables (age, AUDIT score) and 2‐sided χ^2^ tests (or Fisher's exact test for rare events) for categorical variables (sex, ethnicity, education, occupation, income and COVID‐19 survey measures).

ANOVAs are generally considered robust against small deviations from the normality assumption with only a small effect on the type I error rate [54]. However, if there is evidence of significant deviation we will attempt to resolve this with transformations (e.g. logarithmic or square‐root transformations) or choose the nonparametric Kruskal‐Wallis H test, which does not require the assumption of normality.

#### Analysis of primary and secondary outcomes

The primary analysis will use a conservative intention‐to‐treat approach to missing data with the assumption of no change for participants who do not respond to follow‐up (i.e. analysis of outcome data from all randomised participants). The effect of group allocation on the primary outcome, change in weekly alcohol consumption, will be examined with an adjusted regression model, adjusting for baseline consumption [55, 56, 57].

A secondary analysis will be conducted to assess differences in change in weekly alcohol consumption using an unadjusted regression model. Regression models have several statistical assumptions that will be assessed (i.e. the errors of the data are normally distributed and there is equal variances between treatments). The analyses are robust to slight deviations in parametric assumptions, but where large deviations are found data transformations and appropriate non‐parametric tests will be considered.

Additional sensitivity analyses will be conducted for the primary outcome at 6 months: (i) responders‐only (i.e. those who completed the 6‐month follow‐up survey); (ii) using multiple imputation for non‐responders on baseline characteristics (with five imputed data sets [58] combined using Rubin's rules [59]) and assuming a normal distribution with a mean of 0 and SD reflecting the variation in change among responders; (iii) per‐protocol approach whereby only participants who downloaded Drink Less in the intervention group and those who viewed the NHS alcohol advice webpage in the comparator group are included in the analyses, and whereby participants whose treatment was contaminated are excluded; (iv) an instrument variable analysis accounting for non‐use in the intervention group and contamination in the comparator by operationalising the difference in app usage between the two conditions; (v) last observation carried forward; and (vi) assessing the effect of the condition by recruitment source.

Secondary analyses will assess: (i) the secondary outcomes at 6 months using ANOVA and χ^2^ analyses as appropriate and (ii) the change over time in the primary outcome using 1‐ and 3‐month follow‐up data.

Confidence intervals, effect sizes (partial η^2^ for ANOVA analyses, odds ratios for χ^2^ and regression analyses) and exact *P* values will be reported. Bayes factors will be calculated using a half normal distribution to specify the predicted effect (of a 2 UK unit reduction per week) with a peak at 0 (no effect) and the SD equal to the expected effect size with Robustness Regions reported to specify the range of expected effect sizes that support the same conclusion [60].

Finally, interactions will be assessed between group allocation with age, sex, ethnicity, education, occupation, income and COVID‐19 measures (survey and national responses) for primary and secondary outcomes. Where significant interactions are found the findings will be stratified, drawing on the PROGRESS‐Plus framework to explicitly consider health equity between the intervention and comparator group [61].

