### Sample size

A sample size of 5562 participants (2781 in the comparator group and 2781 in the intervention group) is required to detect a mean difference reduction of 2 UK units (16 g of alcohol) in weekly alcohol consumption (the primary analysis) at 90% power with an α of 0.05 and a two‐tailed test. This was calculated using G*Power software [22]. The estimated effect size is in line with the Cochrane review on digital alcohol interventions [5] and is roughly equivalent to that found in face‐to‐face brief interventions [23].

An initial sub‐sample of 26 participants (13 from each group [24]), who consented to a short interview about their experience of the trial, will be selected after the 6‐month follow‐up, as part of the mixed‐methods process evaluation. Participants will be purposively sampled to achieve good diversity in terms of sociodemographic characteristics and with high and low engagement. Data will be analysed and data collection will continue only if thematic ‘meaning’ saturation is not reached (see Analysis). Collection will continue in an iterative process (adding 10 participants at a time) until saturation is reached.

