#### Randomisation

Participants who complete the baseline assessment will be randomised individually to intervention and comparator groups using block randomisation (block size of 50) and a random allocation sequence generated by an online automated algorithm (at a ratio of 1:1). Participants will be blinded to study arm. There will be no involvement of the researchers in the randomisation process, and there will be complete allocation concealment.

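### The primary model validly adjusts for baseline consumption but leaves out other prognostic baseline variables already in hand; adding a few would give a small gain in precision at almost no cost

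*Protocol article*

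**What the plan says.** All references are to the protocol article.

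- **Primary model** (Analysis of primary and secondary outcomes): the effect of allocation on change in weekly consumption "will be examined with an adjusted regression model, adjusting for baseline consumption". An unadjusted model is a secondary analysis. Non-responders are counted as unchanged.
- **Baseline comparison** (Analysis): "The difference between the intervention and comparator groups on baseline characteristics will be assessed using" one-way ANOVA for age and AUDIT score, and chi-square or Fisher tests for sex, ethnicity, education, occupation, income and the COVID-19 survey measures. A following paragraph allows transformation or Kruskal-Wallis where normality fails. Baseline weekly consumption is not among the variables tested.
- **Randomisation**: allocation is individual and 1:1, "using block randomisation (block size of 50") with an automated sequence, concealed and without researcher involvement. No stratification factor is named.
- **Timing of baseline data**: the full AUDIT is part of eligibility screening, age and sex belong to the baseline assessment, and only those who finish that assessment are randomised. Enrolment date is therefore known too.
- **Sample size**: 2781 per arm to "detect a mean difference reduction of 2 UK units (16 g of alcohol) in weekly alcohol consumption" "at 90% power with an α of 0.05 and a two‐tailed test". No standard deviation is given.

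**The concern.** A covariate that predicts the outcome and is measured before randomisation reduces residual variance in a linear model without biasing the treatment contrast. This trial collects several plausible candidates. The article itself treats age, sex and COVID-19 measures as relevant, since it plans interaction analyses on them, and the COVID-19 measures section expects the pandemic to alter drinking. Recruitment starts in July 2020 and runs into 2022, so outcomes may shift with calendar time. Blocks of 50 filled in order of enrolment keep the arms roughly equal within any period. A model without period leaves that variation in the residual although the design has already balanced it.

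The baseline tests raise a separate, smaller matter. Under concealed automated allocation, a difference between arms is due to chance unless the allocation process failed. Whether a chance difference matters depends on its size and on how strongly the variable predicts the outcome, and a p-value measures neither. At stake are a little precision in the primary estimate and the clarity of the baseline table.

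**Working it through.** **Inputs from the article:** 2781 per arm (5562 in total), difference 2 units, 90% power, two-sided α of 0.05; two continuous and five sociodemographic categorical variables tested at baseline; a COVID-19 survey of one gate question plus five follow-up questions.

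**Assumptions, not in the article:** the standard deviation, and the share R² of the remaining variance that added covariates would explain.

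**Step 1. Reproduce the sample size.** Solving for the standard deviation:

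SD = 2 / [(1.960 + 1.282) × √(2/2781)] = 2 / (3.242 × 0.02682) ≈ 23.0 units.

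With SD 23 the normal formula gives 2780 per arm. A noncentral t calculation gives power 0.89998 at 2780 and 0.9001 at 2781, so it first reaches 90% at the stated figure. The sample size is consistent with SD 23, but this is back-solved and not an independent confirmation.

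**Step 2. Add covariates.** Take 23 as the residual SD before the extra covariates. Then SD′ = 23 × √(1 − R²), SE = SD′ × √(2/2781), power = Φ(2/SE − 1.96), and half-width = 1.96 × SE.

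| Extra R² | SD′ | Power | 95% CI half-width (units) |
|---|---|---|---|
| 0 | 23.00 | 90.0% | 1.21 |
| 0.01 | 22.88 | 90.3% | 1.20 |
| 0.02 | 22.77 | 90.6% | 1.20 |
| 0.05 | 22.42 | 91.4% | 1.18 |

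As equivalent participants: 5562/0.99 − 5562 ≈ 56 at R² 0.01, and 5562/0.95 − 5562 ≈ 293 at R² 0.05.

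**Step 3. Cost if the covariates explain nothing.** July 2020 to March 2022 spans 7 calendar quarters, and to May 2022 it spans 8, so period takes 6 or 7 parameters. AUDIT score, age and sex as linear or binary terms add 3, giving at most 10. Residual degrees of freedom fall from 5562 − 3 = 5559 to 5549. Variance inflation is about 10/5559 ≈ 0.2%, which costs about 0.05 percentage points of power.

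**Step 4. Baseline tests.** Counting the COVID-19 survey once gives 2 + 5 + 1 = 8 tests; counting all six items gives 2 + 5 + 6 = 13. Under correct randomisation and independence:

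- 8 tests: 1 − 0.95⁸ = 0.34
- 13 tests: 1 − 0.95¹³ = 0.49

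At this sample size p < 0.05 needs a standardised difference of only 1.96 × √(2/2781) ≈ 0.053. For a proportion near 50%, it needs 1.96 × √(0.25 × 2/2781) ≈ 2.6 percentage points.

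**The case against.** The strongest reply is that nothing here is an error. The model is pre-specified and unbiased under randomisation, and the baseline value of the outcome is normally its best single predictor. No stratification factor is omitted, because none is named. An article may also leave a longer covariate list to the analysis plan, which is to be finalised before analysis. All of this stands, so the covariate point is an improvement and not a defect. A reader might infer that adjusting for baseline consumption alone is wrong, or that substantial precision is lost. The documents support neither.

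The gain may also fall short of the range shown. AUDIT score overlaps with the consumption items from which the outcome is derived, and so adds less once baseline consumption is in the model. Setting non-responders to no change probably weakens the covariates further. Pandemic timing is not ignored either: COVID-19 measures and national responses enter the interaction analyses. That examines effect modification, but it does not place period in the primary model.

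On the baseline tests, a reader might infer that they are worthless or that they endanger the result. Both go too far. A gross difference could reveal a failed allocation algorithm, and because data from people who opt out are deleted, the compared set may not be exactly the randomised set. Nothing in the article uses the tests to choose covariates or to qualify the primary result. Independence is also generous: the COVID-19 follow-up questions depend on one gate question, and education, occupation and income are related, so 49% is probably too high. What remains is that the p-values do not show whether an imbalance matters.

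**Conclusion.** The point holds as a modest, nearly free improvement. Adjustment for baseline consumption is valid, and a few further pre-randomisation covariates could sharpen it. With an assumed SD of 23 units and an assumed extra R² of 1–5%, nominal power rises by about 0.3 to 1.4 percentage points and the interval half-width narrows by at most about 0.03 units. The article gives no correlation between these covariates and the outcome, so the gain could be close to zero; the loss if they explain nothing is negligible.

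Replacing the balance tests with descriptive summaries is sound reporting practice and secondary to this. It leaves the primary estimate unchanged.

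**What to change.** 1. In Analysis of primary and secondary outcomes, or in the analysis plan before it is finalised, name baseline AUDIT score, age, sex and enrolment period (calendar quarter) as fixed covariates in the primary model beside baseline consumption. Keep the unadjusted model as the planned secondary analysis.
2. In Analysis, remove the between-arm significance tests of baseline characteristics. Report descriptive summaries by arm, including baseline weekly consumption.
3. Drop the transformation and Kruskal-Wallis fallback for those baseline comparisons only. Secondary outcomes are also to be analysed by ANOVA, and the fallback should remain available for them.

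The cost is wording. No new data are needed, and at most about 10 degrees of freedom of 5559 are used. The covariates must be fixed before outcome data are analysed, so that they are not chosen by their effect on the result.

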**Figure 2 add15287-fig-0002:**
[figure not shown]
Flowchart of procedure

**Table 1 add15287-tbl-0001:** Schedule of enrolment and follow‐up assessments

Assessment	Time‐point			
	Baseline	1 month	3 months	6 months
Informed consent	x			
Eligibility screening	x			
Randomisation	x			
Intervention/comparator initiation	x			
Sociodemographic characteristics^a^	x			
Weekly alcohol consumption	x	x	x	x
AUDIT score and proportion of hazardous drinkers	x			x
Alcohol‐related problems or consequences and alcohol‐related injury				x
Use of healthcare services				x
Health‐related quality of life				x
Psychological measures	x			x
Engagement	x	x	x	x
Acceptability				x
Adverse events		x	x	x
Debriefing				x

^a^

Sociodemographic characteristics include: age, sex, ethnicity, education, occupation, income.

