#### Follow‐up assessments

Follow‐up assessments will be conducted 1, 3 and 6 months after baseline. The 6‐month follow‐up assessment will assess the primary and secondary outcome measures and psychological measures; the follow‐up assessments at 1 and 3 months will assess the self‐reported weekly alcohol consumption only. Participants will have up to 30 days to complete each survey to maximise data retention. Participants will be sent up to three automated emails with a link to a web‐based survey for the follow‐up assessments on days 0, 5 and 9. Participants who do not complete the web‐based follow‐up assessment will be sequentially offered opportunities to do so via phone (called once per day on days 10–17), mailed survey (on day 18) and by postcard (on day 30). Participants will be compensated with gift vouchers of up to £36 for completing the three surveys: £6 for the survey at 1 and 3 months; £12 at 6 months with an additional £12 if the 6‐month survey is completed within 24 hours.

At the 6‐month follow‐up, participants will indicate whether they are happy to be called for a short interview about their experience of the trial; there is no additional compensation for this telephone interview. Acceptability will then be measured after the 6‐month follow‐up via telephone interviews.

Participants will be asked whether they experienced any unexpected consequences, adverse events or other harms from participating in the study (in an open‐ended question at the 1‐, 3‐ and 6‐month follow‐up) and whether they have used any other forms of support for alcohol reduction (at the 6‐month follow‐up).

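### Sensitivity analysis (ii) fixes five imputations and names only baseline predictors: a minor weakness that makes a borderline p-value depend on the seed if non-response is substantial

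*Protocol article*

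**What the plan says.** The Protocol article, under Analysis of primary and secondary outcomes, analyses all randomised participants "with the assumption of no change for participants who do not respond to" follow-up. Six sensitivity analyses of the 6-month primary outcome follow. Item (ii) is the only one that uses multiple imputation. It imputes non-responders from their baseline characteristics "with five imputed data sets [58", pools by Rubin's rules, and adds "assuming a normal distribution with a mean of 0 and SD reflecting the variation in change among responders".

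The number of imputations is therefore stated, and so is the set of variables imputed on. The word 'only' does not appear, but no post-baseline variable is named.

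The section on follow-up says that "assessments will be conducted 1, 3 and 6 months after baseline", and Table 1 schedules "Weekly alcohol consumption" at each of these visits. Elsewhere in the same analysis section, item (v) is "last observation carried forward", and a secondary analysis covers change over time using the 1- and 3-month data.

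**The concern.** A pooled multiple-imputation estimate carries random error from the finite number of imputations. With few imputations and much missing data, that error is no longer small beside the standard error, and the reported p-value then depends partly on the seed. The plan promises exact P values, so the variation would reach print. A borderline result could be called robust or not robust for no reason in the data.

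Item (ii) also leaves unnamed the repeat measurements of the same outcome. For a participant who answered at 1 or 3 months and then dropped out, these are natural predictors of the missing 6-month value.

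**Working it through.** **Inputs from the document.** Difference 2 units per week, 90% power, two-sided 0.05, 2781 per arm (Sample size); five imputations, and draws with mean 0 and the responders' SD (item ii).

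**Assumptions.** Non-response of 10%, 20% or 30%, equal in both arms. The SD of change is not stated.

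**The plan's own figure.** Solving n = 2·SD²·(1.960 + 1.282)²/2² for n = 2781 gives SD = 2/[3.2415·√(2/2781)] = 23.0. With SD 23, a t-test at 2781 per arm has power 0.900. This agrees with the stated sample size but does not check it independently, because the SD was solved from it.

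**Noise under the mean-0 reading, without baseline adjustment.** Let f be the missing fraction.
- Within-imputation variance: W = 2·23²/2781 = 0.380.
- Between-imputation variance: B = f²·2·23²/(f·2781) = f·W.
- Long-run standard error: √[W(1 + f)].
- Monte Carlo SD of the pooled estimate: √(fW/m).
- Their ratio: √{f/[m(1 + f)]}.

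| Missing | Long-run SE | Monte Carlo SD, m = 5 | Ratio, m = 5 | Ratio, m = 50 |
|---|---|---|---|---|
| 10% | 0.65 | 0.09 | 0.13 | 0.04 |
| 20% | 0.68 | 0.12 | 0.18 | 0.06 |
| 30% | 0.70 | 0.15 | 0.21 | 0.07 |

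**Effect on p.** The responder data were held fixed so that the long-run p is 0.035. The imputations were redrawn many times and pooled by Rubin's rules with their t reference distribution.

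| Missing | m | p, 5th to 95th percentile of seeds | Seeds with p > 0.05 |
|---|---|---|---|
| 20% | 5 | about 0.014 to 0.094 | 34% |
| 20% | 50 | 0.027 to 0.046 | 2% |
| 20% | 100 | 0.029 to 0.043 | 0.1% |
| 30% | 5 | about 0.012 to 0.115 | 39% |
| 30% | 50 | 0.025 to 0.050 | 5% |
| 30% | 100 | 0.028 to 0.045 | 0.8% |

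**Away from the threshold, m = 5.** With a 2-unit effect in responders, 8% of seeds exceed 0.05 at 20% missing and essentially none at 10%. With 2.5 units at 20% missing the share is 0.1%. At 10% missing a borderline result can still cross: with long-run p 0.033, 17% of seeds do.

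**The other reading.** If item (ii) means regression imputation on arm and baseline, the ratio is about √(f/m): √(0.2/5) = 0.20 and √(0.3/5) = 0.24. A separate simulation used 300 seeds (100 at m = 50), an assumed baseline-change correlation of -0.4 and values missing completely at random. At 30% missing and a responder effect of 1.6 units, p ran from 0.003 to 0.104 at m = 5 and from 0.010 to 0.031 at m = 50 (central 95%). At 20% missing and 2.0 units, all 300 seeds gave p < 0.05 at m = 5.

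**Value of the interim data.** Suppose a share a of non-responders has interim data that correlate r with the 6-month change. The fraction of missing information falls roughly from f to f(1 - a·r²). With a of 0.3 to 0.5 and r of 0.5 to 0.7 (both assumed), 0.30 falls to between 0.30·(1 - 0.3·0.25) = 0.28 and 0.30·(1 - 0.5·0.49) = 0.23, and 0.20 falls to between 0.19 and 0.15. None of this applies while imputed changes are drawn around 0, because predictors then do not move the imputed mean.

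**The case against.** Four points on the other side carry weight.

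- **Five imputations are inefficient, not invalid.** Rubin's rules already include the 1 + 1/m term and reduced degrees of freedom. Relative efficiency, 1/(1 + f/m), is 96% at f = 0.2 and 94% at f = 0.3. Part of the share above 0.05 is this built-in conservatism: at 30% missing and long-run p 0.035, the median p at m = 5 is 0.041. This stands, but does not remove the seed dependence.
- **The threshold case is chosen.** A reader might infer that two analysts would generally reach opposite conclusions about robustness. The figures do not support that away from 0.05. A 2-unit effect can nonetheless fall near the threshold: at 30% missing with mean-0 draws its long-run p is about 0.047. There even 100 imputations split about 31/69 across 0.05, so the mean-0 draw matters more than the number of imputations.
- **The interim data are not ignored.** A reader might infer that the 1- and 3-month outcomes go unused. That is true of item (ii) as worded, but last observation carried forward and the change-over-time analysis may use them. Carrying a value forward does not do the work of an imputation model, since it adds no imputation uncertainty.
- **The article is condensed.** The final analysis plan, to be uploaded before analysis, may list further predictors and a seed. The stated number of five would still have to be changed.

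A reader might also take 20-30% non-response as the trial's expectation. The Discussion names retention as a main challenge and refers to follow-up in other trials, but gives no rate.

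**Conclusion.** The point holds as a minor one. Five imputations are too few if non-response reaches about 20-30%: the noise is about a fifth of a standard error, enough to move a borderline p-value across 0.05 in roughly a third or more of seeds. At 10% missing the noise falls to about 0.13 of a standard error, and for clear results at any of these rates the reading hardly changes.

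This is one of six sensitivity analyses, so the primary no-change analysis and its conclusion are untouched. Naming the interim data would probably bring a modest gain, and none under the mean-0 draw as written. The sizes rest on the assumed missing fractions, the back-solved SD of 23 and, for the interim data, assumed correlations and availability.

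**What to change.** In the final analysis plan:

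1. Replace five with at least 50 imputations (100 is a safe choice) and state the seed in advance.
2. Put arm, baseline consumption and the observed 1- and 3-month consumption in the imputation model.
3. Reconcile the mean-0 draw with imputation from predictors. One way is to make the predictor-based imputation item (ii) and keep the mean-0 draw as a separate scenario, labelled as assuming no average change in non-responders. Without this step, the second change has no effect on the imputed means.

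The cost is a changed number, a longer predictor list, one clarified sentence and minutes of computing. No extra data are needed.
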